A stratified approach to rehabilitation after hip fracture was subsequently developed. First, we developed and validated a subgrouping tool 'the stratify hip algorithm' (based on three multivariable prediction models) to identify patients at low-, intermediate- and high-risk of death and/or change in residence (to a higher level of care) using records for over 170,000 patients admitted to one of 173 hospitals in England and Wales. The approach requires entry of 5 pieces of information to a website: <https://stratifyhip.co.uk/> (age, sex, prefracture mobility, prefracture residence, and dementia diagnosis) to subgroup each patient. Overall, 31% of patients were assigned low-risk, 28% medium-risk, and 41% high-risk across three outcomes (in-hospital death, change in residence, 30-day death). Patients in the overall low-risk subgroup were typically less than 80 years old with the majority female (66%), admitted from home (91%), with outdoor mobility pre-fracture (83%), and no dementia diagnosis (95%). Compared to the overall low-risk subgroup, a greater proportion of patients in the overall medium-risk subgroup were older (94% aged 80 years or more), female (99%), and had a dementia diagnosis (14%). Compared to the overall medium-risk subgroup, patients in the high-risk subgroup were of a similar age (94% aged 80 years or more); however, a greater proportion was male (37%), with indoor/no mobility (69%), admitted from nursing/residential care (40%) with a dementia diagnosis (50%).

Next matched interventions were designed for each subgroup identified by the algorithm. These interventions were informed by qualitative interviews with patients, physiotherapists, and the multidisciplinary team, an umbrella review of systematic reviews of older adults who underwent rehabilitation interventions in the acute setting, recent systematic (including Cochrane) reviews, international guidelines, consultation with our public and patient involvement group 'TROOP' (further detail of TROOP available at [www.ppitroop.co.uk](http://www.ppitroop.co.uk)), and an intervention development workshop and survey (following a nominal group technique) to prioritize intervention components with key stakeholders.

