### **7.2 Screening Procedures**

An anonymous screening log will document the number of adults admitted with hip fracture, the number screened (the number ineligible and reasons for ineligibility, and reasons for eligible but not screened), the number ineligible after subgroup assignment (we will target enrolment of 20 participants to each subgroup), the number approached, and the number who declined (and why). For those eligible but declined, we will also retain data on their subgroup assignment to determine whether the rates of decline vary by subgroup. The screening log will be completed by the clinical team who would routinely treat/access this cohort of patients to ensure the common law duty of confidentiality will be upheld. A site principal investigator (PI) who would routinely treat/access this cohort of patients will be responsible for ensuring the accuracy of the log.

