## **7.4 Randomisation procedures**

The randomisation approach was designed with a statistician (SA) and validated for use prior to implementation. Once a participant has provided informed consent, they will be allocated a participant identification number (PID). Baseline data will subsequently be collected by the research team prior to randomisation. Randomisation will follow a 1:1 random allocation sequence stratified by subgroup assignment (low-, medium-, high- risk), using a secure internet-based system, developed and maintained by King's Clinical Trials Unit to ensure allocation concealment. Treatment allocation will be revealed (after randomisation) to a member of the research team, linked to the participant number, and the clinical team will be notified.

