## **7.6 Schedule of assessments for each visit**

Participants will undergo screening, baseline assessment, assessment at intervention end, and assessment at 12-weeks post-randomisation. Assessments at baseline and intervention end will be in-person, over the telephone, or via MS TEAMS (the mode will be documented). Assessments at 12-weeks post-randomisation will be completed over the telephone or via MS TEAMS.

Screening for eligibility: Confirmation planned surgical intervention for hip fracture and aged 60 years or more. Additional assessment prior to consent will include a member of the direct care team's determination of capacity, confirmation whether the potential participant is enrolled in any other study, and subgroup assignment (to ensure no more than 12 participants from one subgroup enrolled to each arm of the study).

Baseline: Following consent and prior to randomisation, a member of the research team will collect the following participant characteristics: age, sex, ethnicity, fracture type, surgery type, Abbreviated Mental Test, Mini Nutritional Assessment, hospital concerns about falls

assessment, pre-fracture residential status (home, residential home, nursing home), living status (lives alone, with independent spouse, with dependent spouse, with family, with other), prefracture mobility. They will also collect patient-reported outcome measures which satisfy the core outcome set for hip fracture trials:

- a) health-related quality of life (EuroQoL EQ-5D-5L)
- b) activities of daily living (Barthel Index; Nottingham Extended Activities of Daily Living)
- c) falls related self-efficacy (Short Falls Efficacy Scale-International)
- d) pain (Numeric Rating Scale)
- e) walking ability (New Mobility Score)

A bespoke resource use data collection form will also be collected. This form can be collected both prior to and/or after randomisation but will be completed prior to discharge (and intervention end).

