## **14 STATISTICAL CONSIDERATIONS**

### **14.1 *Sample size***

The sample size was determined in consultation with the trial statistician. The recruitment target of 60 participants aims to have sufficient participants to provide the operational experience to plan a definitive trial; provide reasonably robust estimates of our feasibility outcomes; and to estimate the variability of the proposed patient outcomes to inform a future sample size calculation. A recruitment target of 60 participants (30 per treatment arm) will allow overall retention rate at 12-weeks to be estimated with precision of  $\pm 11\%$ , using an exact 95% confidence interval, from previously observed retention rates of  $\sim 80\%$  for the same population. Assuming a non-differential retention rate of 80% at 12-week follow-up, this target will provide follow-up outcome data on  $\sim 24$  participants per arm.

This required sample size will be attainable in practice. In 2022, 255 patients were admitted to a hospital ward at St Thomas's Hospital with hip fracture. Previous trials of patients with hip fracture reported recruitment rates of 32% in hospital.

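### The subgroup limits in 7.2 and 7.6 leave the closing point undefined, the per-arm limit cannot be checked before consent, and patients refused on quota are logged as ineligible with no rule for counting them in Figure 2

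*Protocol*

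**What the plan says.** - **Subgroup target.** Protocol 7.2 defines a screening-log count: "the number ineligible after subgroup assignment (we will target enrolment of 20 participants to each subgroup". The target appears in the definition of that count, so a full subgroup is evidently the reason for it.
- **Subgroup ceiling.** Protocol 7.6 lists subgroup assignment among the checks made before consent, with the purpose "to ensure no more than 12 participants from one subgroup enrolled to each arm of the study". The sentence begins "Additional assessment prior to consent will include a member of the direct care team's determination of capacity", so the timing is explicit.
- **Allocation.** Protocol 7.4 describes a "1:1 random allocation sequence stratified by subgroup assignment", run in a concealed central internet-based system. After each randomisation a research team member learns the allocation and the clinical team is notified.
- **Who does what.** In Table 1, site therapists complete the screening and subgroup logs and deliver treatment in both arms.
- **Eligibility.** Sections 6.1 and 6.2 contain no subgroup quota.
- **Progression.** In Figure 2, 40% or more eligible is GO and 21–39% is AMEND. For recruitment, 50% or more of the eligible recruited is GO, 31–49% AMEND and 30% or less STOP. Neither row says where a patient refused on quota belongs.
- **Population mix.** The Introduction reports that "31% of patients were assigned low-risk, 28% medium-risk, and 41% high-risk".

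**The concern.** Three things are left loose.

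1. **Closing point.** When the 21st patient of a subgroup is screened, 7.2 suggests refusal and 7.6 allows enrolment. Site staff cannot tell which applies.
2. **Per-arm wording at a step with no arm.** Before consent, only the subgroup total can be controlled. If staff tried to follow 7.6 literally they would have to count past allocations by arm. Once one arm of a subgroup held 12, every later allocation in that stratum would be forced. The clinical team that screens also learns the allocations, so it could predict them.
3. **The label.** A full subgroup is a feature of this pilot, not of the patient. If these refusals are counted as ineligible, they lower a rate that decides GO or AMEND, although the definitive trial may have no such quota. If they are counted as eligible but not recruited, they lower the other rate. The rule needs to be fixed before the rates are seen.

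**Working it through.** **Inputs from the protocol.** Total 60, 30 per arm (14.1). Target of 20 per subgroup (7.2). Limit of 12 per subgroup per arm (7.6). Mix 31/28/41 (Introduction). Recruitment rate 32% in earlier trials (sections 6 and 14.1). GO at 40% eligible and at 50% of eligible recruited (Figure 2).

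**Assumptions.** The 31/28/41 mix, which comes from data for England and Wales, holds at this site. Acceptance is 32% in every subgroup. Recruitment stops at 60.

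**Step 1: the totals.**
- 3 × 20 = 60, which reproduces the recruitment target.
- 2 × 12 = 24 per subgroup, and 3 × 24 = 72 in all.
- With 60 enrolled, 20/20/20 satisfies both passages. A split of 24/24/12 satisfies 7.6 but misses the target in 7.2.

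**Step 2: how many are refused.** Simulated enrolment to 60, with a subgroup closed when its total reaches the limit. The first row counts all otherwise eligible patients seen until the 60th enrolment.

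| | Close at 20 | Close at 24 |
|---|---|---|
| Otherwise eligible patients screened (mean) | about 241 | about 198 |
| Refused because subgroup full (mean share) | about 21% | about 5% |
| Smallest subgroup (mean) | 20 | 16 |
| Smallest subgroup (5th percentile) | 20 | 12 |

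For the close at 20, the 10th to 90th percentile of the refused share is 9% to 34%.

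Cross-check: counting only willing patients, about 77.3 are needed at a close of 20 and 63.4 at a close of 24. Dividing by 0.32 gives 77.3 / 0.32 ≈ 241.6 and 63.4 / 0.32 ≈ 198.1, in agreement with the table.

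**Step 3: effect on the eligibility criterion, if refusals count as ineligible.** Observed rate = true rate × (1 − refused share). The true rate needed to show 40% is 0.40 / (1 − share).
- Close at 20: 0.40 / (1 − 0.21) ≈ 0.51.
- Close at 24: 0.40 / (1 − 0.05) ≈ 0.42.

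A true rate between 40% and these values would read as AMEND. For example, a true 45% reads as 0.45 × 0.79 ≈ 36% (AMEND) at a close of 20, and 0.45 × 0.95 ≈ 43% (still GO) at a close of 24.

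**Step 4: effect on the recruitment criterion, if refusals count as eligible in its denominator.** At a close of 20, 32% becomes 0.32 × 0.79 ≈ 25%. The simulated mean is about 26%, and 86% of runs fall at or below 30%. That moves the result from AMEND to STOP. Relabelling the refusals as eligible without also removing them from this denominator would only move the bias from one criterion to the other.

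**The case against.** **A target and a ceiling do not conflict.** This stands. One passage gives an aim and the other a maximum, and 12 per arm reads naturally as tolerance around 10. A reader might infer that the two passages contradict each other. They do not, and 72 is only the sum of the ceilings, because the total is fixed at 60. What remains is that neither passage states when a subgroup closes.

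**Allocation concealment is not shown to be broken.** This also stands. A reader might infer that the per-arm limit cannot be applied without exposing allocations. Allocation sits in a concealed central system; a limit could be held inside it, or a subgroup could be closed on its total, and nothing would be exposed. No passage tells therapists to count by arm. The risk is conditional on staff enforcing the wording of 7.6 as written.

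**Chance imbalance.** It is tempting to work out how often an arm would pass 12 under simple randomisation. The protocol does not say that allocation is unblocked, and block details are properly kept out of a protocol, so such a figure would describe a design the document does not state.

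**The refusals are a separate count in the log.** True: 7.2 lists them apart from other ineligibility, so the data can be separated afterwards. Nothing states that they count against the 40% line. But the log calls them ineligible and Figure 2 is silent, so the label is the natural default.

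**The 21% belongs to a hard close at 20.** True, which is why both closing points are shown.

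**Equal subgroups are deliberate.** Section 6.1 wants the intervention assessed in all three risk groups, and 14.3 already summarises baseline, outcome and fidelity data by subgroup. A reader might infer that overall rates must be re-weighted to the population mix; that is a reporting choice, not an error in the protocol.

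**Conclusion.** The point holds as a matter of undefined rules. The protocol leaves the subgroup closing point open between 20 and 24, words the limit by arm at a step where no arm exists, and labels quota refusals ineligible without an eligibility criterion that makes them so or a rule for counting them in Figure 2.

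The progression decision is where this matters most. Under the stated assumptions, and only if the label is followed, true eligibility of 40% to about 51% (close at 20) or 40% to about 42% (close at 24) would be read as AMEND instead of GO. The figures depend on the mix at this site and on equal acceptance across subgroups, and individual runs vary widely. The documents do not support reading this as a contradiction between the quotas or as an established loss of concealment. It should be corrected, since the change is cheap and protects a decision rule.

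**What to change.** - **7.6:** replace the per-arm wording with one cap on the subgroup total, consistent with 7.2 and checked without reference to arm. Say in 7.2 whether its figure is that cap.
- **7.2 and the screening log:** record 'subgroup full' under its own code, not as ineligible.
- **Figure 2:** count these patients as eligible for the 40% eligibility criterion, and exclude them from the denominator of the 50% recruitment criterion. Both halves are needed, as Step 4 shows.

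Cost: edits to two sections and one figure, and one log code. The number randomised stays at 60. Closing at 20 rather than 24 secures equal subgroups but means more screening, about 241 against about 198 otherwise eligible patients under the assumptions above. For scale, the site had 255 hip fracture admissions in 2022 (14.1).

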| Carer education                                | Categorical            | Carer interview                  | Research team  |  |   |   | X |   |   |
| Carer children                                 | Binary                 | Carer interview                  | Research team  |  |   |   | X |   |   |
| Carer employment status                        | Categorical            | Carer interview                  | Research team  |  |   |   | X |   |   |
| Carer relationship to participant              | Categorical            | Carer interview                  | Research team  |  |   |   | X |   |   |
| Treatment - control                            | -                      | -                                | Site therapist |  |   |   | X |   |   |

|                                       |                                    |                         |                |  |  |  |   |   |   |
|---------------------------------------|------------------------------------|-------------------------|----------------|--|--|--|---|---|---|
| Treatment - intervention              | -                                  | -                       | Site therapist |  |  |  | X |   |   |
| Treatment observations                | Binary, categorical, and free text | Questionnaire           | Research team  |  |  |  | X |   |   |
| Treatment logs                        | Categorical                        | Therapist questionnaire | Site therapist |  |  |  | X |   |   |
| Deviation log                         | Free text                          | Therapist questionnaire | Site therapist |  |  |  | X |   |   |
| Patient diary                         | Categorical                        | Patient diary           | Patient/carer  |  |  |  | X |   |   |
| Length of stay                        | Numerical                          | Patient notes           | Site therapist |  |  |  |   | X |   |
| Mortality                             | Binary                             | Online death records    | Research team  |  |  |  |   | X | X |
| Readmission                           | Binary                             | Patient interview       | Research team  |  |  |  |   |   | X |
| Readmission diagnosis (as applicable) | Free text                          | Patient interview       | Research team  |  |  |  |   |   | X |
| Completion logs                       | Binary                             | Therapist questionnaire | Site therapist |  |  |  |   | X | X |

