### **7.3 Recruitment**

Participants will be recruited within 4 days of admission to a hospital ward at St Thomas's Hospital with hip fracture. This is to allow sufficient time to deliver the intervention, given the average length of stay after hip fracture is 16 days. Recruitment of this patient population within this timeframe has been completed successfully in previous UK trials. Patients may be recruited pre- or post- operatively. In the rare instance where a patient is recruited pre-operatively but then does not go on to have surgery, they will be removed from the trial and replaced.

A member of the direct care team will decide whether a potential participant has capacity to give informed consent.

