fidelity (inclusive of barriers and facilitators to implementation) will be conducted. Interviews will target 100% of therapist involved in delivery of the intervention arm but continue until no new themes are identified.

**12-week follow-up:** At 12-week follow up, a member of the research team will collect data related to mortality (death records will be checked online prior to contacting the participant/their carer), readmissions (and admitting diagnosis), place of residence (home, residential home, nursing home), and living status (lives alone, with independent spouse, with dependent spouse, with family, with other), any adverse/serious adverse events, as well as the following patient-reported outcome measures:

- a) health-related quality of life (EuroQoL EQ-5D-5L)
- b) activities of daily living (Barthel Index; Nottingham Extended Activities of Daily Living)
- c) falls related self-efficacy (Short Falls Efficacy Scale-International)
- d) pain (Numeric Rating Scale)
- e) walking ability (New Mobility Score)
- f) bespoke resource use data collection form (including health and social care, informal care and paid/unpaid work)

Participants who are non-English language speakers will be supported to complete assessments (except patient reported outcome measures) with the use of language support at the Trust. Patient-reported outcome measures which have an established translated, validated, and (where applicable) culturally adapted version in the appropriate language will be circulated by post to the participant with a pre-paid envelope for return direct to the research team.

For carers recruited to the study, we will collect data relating to their age, sex, education, employment (not employed, part-time, full time), children (yes, no), and relationship to the participant. A member of the research team will purposively sample participants who are carers of those assigned to different risk subgroups (low, medium, high) for telephone/MS TEAMS semi-structured interviews focused on treatment acceptability and fidelity (inclusive of barriers and facilitators to implementation). Interviews will target 50% of intervention carers but continue until no new themes are identified.

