## 10 ASSESSMENT OF SAFETY

Participant safety will be determined through the reporting of AE and SAE which will be coded in MedDRA. The period for AE reporting will be following the signing of the study consent form until final follow-up at 12-weeks.

**An adverse event (AE)** is defined as any untoward medical occurrence in a study participant, which does not necessarily have a causal relationship with the trial intervention. Adverse events that will be collected and reported in this trial are limited to:

1. an exacerbation of a pre-existing illness.
2. an increase in the frequency or intensity of a pre-existing episodic event or condition.
3. continuous persistent disease or a symptom present at baseline that worsens following administration of the trial intervention.

**A serious adverse event (SAE)** is defined as an untoward occurrence that:

1. results in death.
2. is life threatening (at the time of the event).
3. requires unplanned hospitalisation or prolongation of existing hospitalisation.
4. results in persistent or significant disability or incapacity.
5. Other 'important medical events' may also be considered serious if they jeopardise the participant or require an intervention to prevent one of the above consequences.
6. Results in a congenital anomaly or birth defect

NOTE: The term "life-threatening" in the definition of "serious" refers to an event in which the participant was at risk of death at the time of the event; it does not refer to an event which hypothetically might have caused death if it were more severe.

All deaths occurring from randomisation until final follow-up (12-weeks) or withdrawal from the study, irrespective of their relationship to the intervention, will be documented by a notification of death form and entered into the trial database within 24 hours of identifying the death. Cause of death will be recorded where available.

For the current intervention, prolongation of existing hospitalisation following a fall may be an expected SAE and related to the intervention, given the intervention encourages people to increase their exercise, mobility, and/or activities of daily living. A related and unexpected SAE is an event which is related to the intervention; and 'unexpected' – that is, the type of event is not listed in the protocol as an expected occurrence.

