Where AEs/SAEs occur, the team (direct care team delivering the intervention and control arms) will follow Good Clinical Practice Guidelines for the reporting to the medical team responsible for the participant's care and notify the Principal Investigator (PI). PIs at all sites will report all AEs/SAEs to the CI via the study electronic database (REDCap). The CI will review all AEs/SAEs against GSTFTs guide for assessment of whether the event is related

to the intervention or not. The CI will then be responsible for reporting SAEs to the Sponsors R&D office.

All SAEs that are to be reported to the R&D office will be signed and dated and completed by the CI. Where a related and expected SAE occurs that does not require immediate reporting, this SAE will be reported in the Annual Progress Report and copied to the R&D office, alongside any AEs that occur that are not classified as 'serious'.

Related and unexpected SAEs will be reported immediately upon knowledge of the event to the R&D office and always within 24 hours. Reports of related and unexpected SAEs will be submitted to the Main NHS/ HSC REC within 15 days of the Chief Investigator becoming aware of the event, using the appropriate template. The form will be completed in typescript and signed by the Chief Investigator. The main REC will acknowledge receipt of safety reports within 30 days. A copy of the SAE notification and acknowledgement receipt will also be sent to the R&D office. The SAE will also be documented as unexpected and related in the CRF, participants medical notes if they are in hospital at the time, annual report (with site copied), and on Datix.

A joint Trial Steering and Data Monitoring Committee (TSDMC) will be informed of the number, nature and review outcomes for all serious adverse events and be asked to recommend any necessary actions.

Where an SAE occurs that does not require immediate reporting, this SAE will be reported in the Annual Progress Report and copied to the R&D office, alongside any AEs that occur that are not classified as 'serious'. The final report will detail the number (events and individuals) and nature of all events (AEs and SAEs) reported to members of each site and/or research team and will be submitted to the REC with the sponsor copied.

Please see Appendix 1 and 2 for further information on reporting of SAEs.

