### **11.2 *Withdrawal / dropout of participants***

Participants are free to withdraw from the trial at any point or a participant can be withdrawn by their consultee or the CI/site PI. No sanctions will follow if the participant (or the consultee on their behalf) decides to leave the research at any time.

Participants (/consultees on the participants behalf) who wish to withdraw will have the option of withdrawal from:

- All aspects of the trial but continued use of data collected up to that point.
- All aspects of the intervention but continued use of data collected up to that point and continue with planned completion of questionnaires and interviews as well as collection of information from routine health records for the purpose of primary and some secondary outcomes.
- Any ongoing aspects of the trial that require patient contact or completion of questionnaires, but permission to collection of information from routine health records for the purpose of primary and some secondary outcomes.

Participants can be withdrawn by the CI/site PI following:

- A change in the health status of the participant that the clinical team report justifies withdrawal.

For participants who die or who are not responsive to attempts to contact for assessments and interviews at intervention end and 12-week follow-up, they will be withdrawn from the trial but the research team will continue to use data collected up to that point, and collect information from routine health records for the purpose of some secondary outcomes. If withdrawal occurs, the primary reason for withdrawal will be documented in the participant's case report form (CRF) (as available). Participants who withdraw will not be replaced.

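### After discharge, non-fatal SAEs and readmissions rest on one recall-based call at 12 weeks, and the records provision in section 11.2 neither covers everyone nor names these outcomes

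*Protocol*

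**What the plan says.** Section 10 fixes the window: "The period for AE reporting will be following the signing of the study consent form until final follow-up at 12-weeks". Unplanned hospitalisation is one of its SAE criteria, so an unplanned readmission is normally an SAE. The AE and SAE count is secondary objective 6.

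After randomisation, sections 7.6 and 7.9 schedule two research contacts: intervention end and 12 weeks. Section 7.7 delivers the intervention during the inpatient stay, so the first of these falls around discharge. For the second, "Assessments at 12-weeks post-randomisation will be completed over the telephone or via MS TEAMS", and at that contact the team collects "any adverse/serious adverse events, as well as the following patient-reported outcome measures".

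Otherwise, section 10 describes one reporting route, in which "the team (direct care team delivering the intervention and control arms) will follow Good Clinical Practice Guidelines for the reporting to the medical team". That team treats participants on the ward.

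Table 1 lists readmission and the row "Readmission diagnosis (as applicable") with the patient interview as source, at 12 weeks only. Mortality comes from online death records at both follow-ups. The 12-week resource use form is a patient questionnaire.

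Section 7.3.2 lets a consultee support or complete data collection. Section 11.2 lets participants who withdraw choose options that keep routine-record collection. For participants who die or cannot be reached, it says the team will "collect information from routine health records for the purpose of some secondary outcomes". It does not say which outcomes those are.

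**The concern.** Most of the safety window lies where the plan has no active observer. Followed as written, a non-fatal SAE or readmission after discharge enters the data if someone remembers it and reports it about ten weeks later, on one call. The protocol's own development cohort had dementia in half of its high-risk patients. The people hardest to reach at 12 weeks may also be those who were readmitted.

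At stake are the AE/SAE count and the readmission outcome. A low count could reflect incomplete collection rather than few events, and it would feed the planning of the definitive trial. The period is not irrelevant to the intervention: the medium-risk discharge plan (section 7.7.2) covers mobility goals to be continued at home. The reporting clocks in section 10 run from awareness, and for such events awareness may come only at the 12-week call.

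The source is also inconsistent. Table 1 allows the interview only, while section 11.2 opens records for some participants. If records are used only for non-responders, events in responders rest on recall and events in non-responders on records.

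**Working it through.** **The plan's own figure.** Section 14.1 gives a precision of ±11% for 80% retention in 60 participants. The exact (Clopper-Pearson) 95% interval for 48/60 is 67.7% to 89.2%, with half-width (89.2 − 67.7)/2 = 10.8 points. The figure is reproduced, as is 30 × 0.80 = 24 per arm.

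**Share of the window after discharge.** Inputs: 84 days (section 10); the recruitment rule, "Participants will be recruited within 4 days of admission to a hospital ward"; and the stay, "given the average length of stay after hip fracture is 16 days" (both section 7.3). I count from randomisation and treat it as falling on the recruitment day. The share is 1 − (stay − recruitment day)/84.
- Day 0: 16 inpatient days remain, so (84 − 16)/84 = 68/84 = 81.0%.
- Day 4: 12 inpatient days remain, so (84 − 12)/84 = 72/84 = 85.7%.
- The share falls below 80% once inpatient days after randomisation exceed 0.20 × 84 = 16.8. A 20-day stay from day 0 gives 64/84 = 76.2%.
- Section 5.1 counts the 12 weeks from discharge, while sections 7.6, 7.9 and 12.1 count from randomisation. On the section 5.1 reading the share is 84/(84 + 16) = 84.0% to 84/(84 + 12) = 87.5%.

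**Length of recall.** 68 to 72 days is 9.7 to 10.3 weeks.

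**Participants without an interview.** 60 × 0.20 = 12, or 6 per arm. Section 11.2 treats people who die as withdrawn, so the 12 may include deaths.

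**Participants with dementia.** Assume 20 per subgroup (section 7.2) and the development-cohort shares in section 2: high 50%, medium 14%, low 5% (the complement of 95% without a diagnosis). Then 20 × 0.50 + 20 × 0.14 + 20 × 0.05 = 10 + 2.8 + 1 = 13.8, about 14 participants.

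**Events that could hinge on section 11.2.** The documents give no SAE rate. Assume that 5% to 30% of participants have a non-fatal SAE or readmission after discharge, independently and at the same rate in those not retained. Among 12 people the expected number affected is 12 × 0.05 = 0.6 to 12 × 0.30 = 3.6. The chance of at least one is 1 − 0.95^12 = 46% to 1 − 0.70^12 = 99%. Whether these are found depends on the unnamed outcomes in section 11.2.

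**The case against.** The case for the plan has real substance.

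- **Deaths are captured.** Online records are checked at both follow-ups, so a reader who inferred that all post-discharge SAEs depend on the interview would be wrong.
- **Proxies can answer.** Consultees may complete data collection, and section 7.6 envisages contact with the participant or carer. It does not follow that events in people with dementia are missed. What remains is proxy recall over about ten weeks.
- **Records are foreseen for non-responders.** AE/SAE counts are a secondary objective, so section 11.2 might be meant to include them. A reader might infer that harms in the 20% are lost, but the text does not establish that. What stands is that section 11.2 never names these outcomes and Table 1 lists no records source for readmission.
- **In-hospital events are covered.** AEs and SAEs are also collected at intervention end, and the one related SAE that section 10 names as expected is prolongation of the existing hospital stay after a fall. The missing AE/SAE row in Table 1 is not a defect in itself, because sections 7.6 and 10 specify collection.
- **It is a small feasibility trial.** Counts are descriptive, and section 13.1 sets no criteria for stopping early, so no formal decision rule turns on a late report.
- **A records check could unblind.** Under section 7.7.2 the falls assessment and discharge plan of medium-risk intervention participants are filed in the medical chart. Section 7.5 requires the AE/SAE assessor to be blind, and the patient-notes items in Table 1 are completed by the site therapist, not the research team. This objection stands and shapes the fix.

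**Conclusion.** The concern holds in a limited form. At the average stay, 81% to 86% of the window falls after discharge, and over that period non-fatal SAEs and readmissions rest on one recall-based contact. The share is lower for longer stays. Under-counting is a risk, not a certainty, and its size cannot be estimated because the documents give neither an event rate nor a recall rate. It is most plausible in the roughly 14 participants who would have dementia, if the trial resembles the development cohort, and among the roughly 12 not retained at 80% retention.

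A reader might also infer a bias between arms. The documents do not support that, since the planned collection is the same in both. The difference they do create is between responders and non-responders, if records are used only for the latter. Data source and safety ascertainment are fixed in the Protocol itself, so this is not a matter to leave to the analysis plan.

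**What to change.** - In Table 1 and section 7.6, make the source for readmission, readmission diagnosis and hospitalisation-type SAEs routine health records plus interview. Apply it at 12 weeks to every randomised participant who has not refused record use, in the same way in both arms.
- In section 11.2, name these outcomes among those taken from records, so that it agrees with Table 1.
- Protect blinding. The site therapist who already completes the patient-notes items extracts only admission dates and diagnoses onto a fixed form without allocation, which goes to the blinded assessor. The therapist may know the allocation, so the form should leave no room for judgement.
- Keep the interview for events at other hospitals, and report the source of each event.
- Reconcile the 12-week anchor between section 5.1 and sections 7.6, 7.9 and 12.1.

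The cost is a short amendment and one brief record check for each of 60 participants, at a single Trust whose notes are already a data source. The consent wording should be checked to confirm that it covers this use. Admissions outside the Trust may still rest on interview.
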